### Sample size calculation

2.7

The formula used to calculate the sample size is as follows, which is based on superiority clinical trial hypothesis test sample size estimation.^[23]^ The sample size was calculated on the basis of expected reduction in NT-proBNP. One previous study suggested that the reducing value for NT-proBNP level in AMI patient treatment with PCI is 32%. Therefore, we assume the reduction in NT-proBNP level as 58% in this study. Given a type I error rate of α = 0.05, type II error rate of β = 0.2, Uα(0.05)=1.65, Uβ (0.2) =1.28. The sample size for 1 arm needs to be 63, resulting in n = 2 × 63 = 126 patients. Considering a dropout rate of 10%, a total of 138 patients need to be allocated to reach the required number of patients for the efficacy analysis. For convenience of randomization, we decided to recruit 140 patients. The formula used to calculate the sample size is as follows:$$\text{n1}={\left(\text{U}\alpha +\text{U}\beta \right)}^{2}\times 2P\times (1-P)/{\left(P1-P2\right)}^{2}=\text{n2}$$

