#### Primary and secondary outcomes

2.8.3

The primary outcome measures of the study are NT-proBNP and left ventricular ejection fraction, which will be measured at baseline and 8 weeks after randomization. Secondary outcomes include plasma levels of microRNA-145, plasma creatine kinase-MB, and CardiaC Troponin I levels in blood samples. At the same time, the trial also observes the occurrence of MACEs defined as the composites of deaths from any cardiac causes, myocardial infarction, and revascularization (PCI or CABG) at 8 weeks after randomization. The efficacy of angina symptoms, Seattle Angina Questionnaire, will be recorded at baseline and 8 weeks after randomization and TCM syndrome efficacy.^[24]^ Items to be measured and the time window of data collection are shown in Table 3.

**Table 3 T3:** Schedule of data collection.

Items	Screening period within 1 wk	Treatment period 4–8 wk	Follow-up period 2–12 mo
Signed informed consent	√		
Inclusion/exclusion criteria	√		
Demographic data	√		
Medical history, course of disease, treatment history	√		
Combined diseases	√		
Concomitant medications	√	√	
LVEF	√	√	
NT-proBNP	√	√	
microRNA-145	√		
CK-MB	√		
cTnI	√		
MACEs			√
SAQ	√	√	
TCM syndrome efficacy	√	√	
Vital signs	√	√	
Blood, urine and stool routine	√	√	
Liver and kidney function	√	√	
Adverse events		√	√

Vital signs: temperature, heart rates, breathing, and blood pressure.

CK-MB = creatine kinase-MB, cTnI = CardiaC Troponin I, LVEF = left ventricular ejection fraction, MACE = major adverse cardiac event, SAQ = Seattle Angina Questionnaire, TCM = Traditional Chinese Medicine.

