### Statistical analyses

2.11

The statistical analyses of primary and secondary outcomes will be conducted in both the intention-to-treat set and the per-protocol set. Primary and secondary endpoint data will be collected for the entire follow-up period for all patients. Patients lost to follow-up will be considered at risk until the date of last contact, at which point they will be censored. In the per-protocol set, patients who undergo randomization but withdraw consent to participate or not treated according to the allocated procedure after randomization will be excluded from per-protocol statistical analyses.

IBM SPSS V17.0 software pack was used for data analysis. The normal distribution of the data was tested with Pearson test. Independent sample *t* test was used for the comparison of data with normal distribution, while Spearman test was used for the comparison of data without normal distribution. Data with normal distribution were expressed as arithmetic mean ± standard deviation, while data without normal distribution were expressed as median value (minimum–maximum). A *P* value between .1 and .05 was considered marginally significant, a *P* value between .01 and .05 was considered significant, .001 and .01 highly significant, and < .001 very highly significant.

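### Section 2.11 names Spearman's rank correlation as the between-arm test for non-normal outcomes and leaves the primary comparison unfixed; a rank-sum test and prespecified baseline-adjusted analyses should replace it

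*Protocol article*

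**What the plan says.** Section 2.11 (Statistical analyses) covers the primary and secondary outcomes and sets out a two-branch rule.

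- The gate: "The normal distribution of the data was tested with Pearson test".
- If normal, an independent-sample t test: this "test was used for the comparison of data with normal distribution".
- If not normal: "while Spearman test was used for the comparison of data without normal distribution".

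The section names no rank-sum test, log transformation, change score or baseline-adjusted model.

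Section 2.8.3 gives the primary outcomes as "NT-proBNP and left ventricular ejection fraction, which will be measured at baseline and 8 weeks after randomization", and Table 3 schedules both in the screening and treatment periods. Section 2.7 adds: "The sample size was calculated on the basis of expected reduction in NT-proBNP". The reference reduction there is 32% and the assumed reduction under YLS is 58% ("we assume the reduction in NT-proBNP level as 58% in this study").

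The one objective that is a question of association is in section 2.3, which relates plasma miRNA to cardiac function.

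**The concern.** Spearman's coefficient describes how two ranked variables move together within one set of patients. Section 2.11 places it in parallel with the t test, so its intended role is to compare YLS with placebo, and it is not a test for that purpose. An analyst following the text has to decide which two variables to correlate. For an outcome measured at baseline and at week 8, the obvious pair is those two measurements, and their correlation says nothing about the treatment. Even when the arm code is used as one of the variables, the output is a coefficient, not a difference or ratio between arms with an interval.

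Three further features leave the primary comparison open:

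- A normality pre-test makes the choice of primary test depend on the trial data, and the name Pearson test does not identify which procedure is meant.
- The analysed quantity, week-8 value or change from baseline, is not stated.
- The trial is sized on a reduction, which needs the baseline, yet no named analysis adjusts for it.

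At stake is whether the primary result is a reproducible estimate of YLS versus placebo, and whether collected baseline data are used.

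**Working it through.** **1. The plan's own size, used below.** Section 2.7 gives P1 = 0.58, P2 = 0.32, so P = 0.45, with Uα = 1.65 and Uβ = 1.28.

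n = (1.65 + 1.28)² × 2 × 0.45 × 0.55 / (0.26)² = 8.585 × 0.495 / 0.0676 = 62.9, rounded up to 63 per arm.

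The stated 63 reproduces with the printed z values. Whether those values and that formula suit the design is a separate matter.

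**2. What a Spearman test returns.** Two readings were simulated with 63 per arm and log-normal NT-proBNP.

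- *Baseline against week 8.* With no treatment effect, and baseline-to-week-8 correlations of 0.3, 0.5 and 0.7, the test was significant at 0.05 in 90% to 100% of trials. It detects that patients resemble themselves over time.
- *Arm coded 0/1 against the week-8 value.* This nearly reproduces the Mann-Whitney p value (for example 0.0214 against 0.0220, and 0.0551 against 0.0555). The two agreed on significance in at least 99.75% of runs.

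Section 2.11 describes neither use.

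**3. What baseline adjustment would gain.**

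From the document: 63 per arm, and reductions of 58% and 32%.

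Assumed, because the documents do not give them:
- the reductions read as a ratio of geometric means
- log-normal values
- log-SD σ of 0.8, 1.0 or 1.2
- baseline-to-week-8 correlation ρ of 0.3, 0.5 or 0.7
- a two-sided 0.05 test

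Ratio = (1 − 0.58)/(1 − 0.32) = 0.42/0.68 = 0.618, and its log is −0.482.

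SE for log ANCOVA = σ × √(2/63) × √(1 − ρ²), where √(2/63) = 0.178. Power = Φ(0.482/SE − 1.96).

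Example with σ = 1.0 and ρ = 0.5: SE = 0.178 × √0.75 = 0.154; 0.482/0.154 = 3.12; Φ(1.16) = 0.88.

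| Analysis | σ = 0.8 | σ = 1.0 | σ = 1.2 |
|---|---|---|---|
| Rank-sum, week-8 values (simulated) | 0.91 | 0.74 | 0.58 |
| Log ANCOVA, ρ = 0.3 | 0.94 | 0.81 | 0.66 |
| Log ANCOVA, ρ = 0.5 | 0.97 | 0.88 | 0.74 |
| Log ANCOVA, ρ = 0.7 | 1.00 | 0.97 | 0.88 |

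The ANCOVA rows are from the formula. Simulation of 4,000 trials per setting gave values within about 0.02 of them (0.97, 0.87 and 0.73 at ρ = 0.5). The error variance is multiplied by 1 − ρ², that is 0.91, 0.75 and 0.51.

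**4. Validity of the unadjusted comparison.** With no treatment effect, the t tests, the Mann-Whitney test and ANCOVA all rejected in 3.8% to 5.7% of simulated trials.

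**5. Change scores.** A t test on log change has its variance multiplied by 2(1 − ρ), which is 1.4, 1.0 and 0.6. Simulated power at ρ = 0.5 was 0.92, 0.76 and 0.62 for the three log-SDs, below ANCOVA in each case.

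**The case against.** The strongest reply is that Spearman is a slip of the pen for a rank-sum test. The sentence is about comparing data and stands beside the t test, so a misnamed Mann-Whitney test is a plausible intention. With the arm coded 0/1 the p value is almost the same. This stands in part. A reader might infer that the trial has no valid primary analysis if NT-proBNP is skewed, and the documents do not support that. They do support that the named test is the wrong one, that no coding is described, and that no effect estimate follows from it.

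A reader might also infer a large power loss from running a t test on skewed raw NT-proBNP. That is not this plan's behaviour. Log-normal data with log-SD 0.8 to 1.2 failed Shapiro-Wilk in 100% of simulated trials. A Pearson chi-square check rejected normality in a single arm in at least 98.9%, and both arms never passed together. Such data would not reach the t-test branch.

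Three smaller replies are fair:

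- A Pearson chi-square goodness-of-fit test of normality exists, so that name is unclear and not shown to be wrong.
- The t test might be meant for change from baseline, given how section 2.7 is framed, so the text cannot be said to ignore the baseline. It leaves the quantity unstated.
- Covariates and transformations are often left to an analysis plan, and an unadjusted randomised comparison is valid. The adjustment is therefore a recommendation.

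None of these replies reaches the central point: the wrong test is printed, not omitted, and nothing else in the article supplies a two-sample rank test.

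**Conclusion.** The point holds as a wrong rule in the stated text. Section 2.11 assigns a rank correlation to the between-arm comparison of any non-normal outcome, including either primary outcome if it fails the check. The unclear normality gate and the unstated analysed quantity mean that the primary analysis is not fixed in advance. The documents do not say that NT-proBNP is skewed, so the error takes effect when the protocol's own non-normal branch is triggered.

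The lack of a baseline-adjusted analysis is a missed efficiency gain, not invalidity. Across the assumed ranges, log ANCOVA has power of about 0.66 to 1.00, against about 0.58 to 0.91 for the rank-sum test. At log-SD 1.0 and correlation 0.5 the gain is from about 0.74 to 0.88. These figures rest on an assumed log-SD, correlation, log-normal shape and ratio of 0.62. Section 2.7 itself enters 32% and 58% as proportions. The direction of the gain is dependable; its size is illustrative.

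**What to change.** Rewrite the testing sentences of section 2.11 before unblinding:

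- **NT-proBNP (primary):** ANCOVA of log NT-proBNP at week 8 on arm and log baseline NT-proBNP, reported as a geometric mean ratio with 95% CI.
- **LVEF (primary):** ANCOVA of week-8 LVEF on arm and baseline LVEF, reported as an adjusted mean difference with 95% CI.
- **Skewed outcomes:** replace Spearman with the Wilcoxon rank-sum (Mann-Whitney) test. It can also serve as a sensitivity analysis for the primaries.
- **Normality pre-test:** delete it as the means of choosing the primary test.
- **Spearman:** keep it only for the association of miR-145 with cardiac function (section 2.3).

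The cost is wording. Baseline and week-8 NT-proBNP and LVEF are already scheduled, no visit or patient is added, and the named software runs these analyses.

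### A marginal-significance band above the planned alpha of 0.05, and two primary outcomes with no joint rule and no decisive analysis set, leave the 5% type I error unprotected

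*Protocol article*

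**What the plan says.** All references are to the protocol article.

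- **Primary and secondary outcomes (2.8.3):** "The primary outcome measures of the study are NT-proBNP and left ventricular ejection fraction", measured at baseline and at 8 weeks. The Abstract names the same pair.
- **Sample size calculation (2.7):** "Given a type I error rate of α = 0.05, type II error rate of β = 0.2". One alpha is given, and only one of the two primaries is used: "The sample size was calculated on the basis of expected reduction in NT-proBNP".
- **Statistical analyses (2.11):** primary and secondary outcomes are to be analysed in both the intention-to-treat and the per-protocol set, with no statement of which one decides. The section then grades P values. Between .01 and .05 is plain significant, with two stronger labels below that. At the upper end, a P "value between .1 and .05 was considered marginally significant".

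No section says whether one or both primaries must succeed. None gives an alpha split or a testing order, and section 2.11 does not state whether P values are one- or two-sided.

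**The concern.** Two statements in the article do not fit together. Section 2.7 plans for a 5% type I error, while section 2.11 attaches a form of the word significant to results between .05 and .1. A primary result of P = .08 fails the planned test, yet the plan gives it a pre-written label that reads as partial success.

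The second part concerns the primary claim. With two primaries, two analysis sets and no rule linking them, there are four primary comparisons, and nothing in the text says which of them settles the question. If a favourable result on either outcome may carry the claim, the error rate for the trial's conclusion is not the 5% applied to each test.

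The Discussion presents the trial as confirming whether YLS improves cardiac function. A trial with no true effect could be reported as positive, or marginally so, on whichever outcome and set came closest.

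**Working it through.** **1. Reproduce the plan's own figure.** Inputs from section 2.7: "Uα(0.05)=1.65, Uβ (0.2) =1.28"; control value, "the reducing value for NT-proBNP level in AMI patient treatment with PCI is 32" per cent; intervention value, "we assume the reduction in NT-proBNP level as 58% in this study". With P = (0.32 + 0.58)/2 = 0.45, the article's formula gives

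n = (1.65 + 1.28)² × 2 × 0.45 × 0.55 / 0.26² = 8.5849 × 0.495 / 0.0676 = 62.86, so 63 per arm.

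This matches the article: "The sample size for 1 arm needs to be 63, resulting in n = 2 × 63 = 126 patients". The 1.65 is the one-sided 0.05 deviate. The 1.28 belongs to β = 0.10, not the stated 0.2. That is a separate matter, but it explains why power below comes out near 90%.

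**2. Either-outcome error within one analysis set, two-sided P values, errors in either direction.** For two independent null tests at level a, the chance of at least one rejection is 1 − (1 − a)².

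- a = .05: 1 − 0.95² = 9.75%
- a = .10 (marginal band counted): 1 − 0.90² = 19.0%

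The documents give no correlation between the two test statistics, so it is an assumption. Bivariate-normal results:

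| Correlation | P < .05 | P < .10 |
|---|---|---|
| 0 | 9.75% | 19.0% |
| 0.3 | 9.5% | 18.5% |
| 0.5 | 9.1% | 17.6% |
| 0.7 | 8.4% | 16.1% |
| 0.9 | 7.0% | 13.6% |

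Zero correlation is the worst case here, which is why the figures are worded as up to.

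**3. Only errors that favour YLS.** With two-sided P values, each test falsely favours YLS with probability a/2.

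- P < .05: 1 − 0.975² = 4.9%, against a nominal 2.5% for one test (4.5% at correlation 0.5)
- P < .10: 1 − 0.95² = 9.75% (8.8% at correlation 0.5)

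These two upper figures assume that benefit on the two outcomes is not negatively correlated. Without that assumption the bounds are 5% and 10%. If P values are one-sided, as the 1.65 might suggest, errors favouring YLS are up to 9.75% at .05 and up to 19% at .10.

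**4. What control would do.**

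- Splitting alpha at 0.025 each: 1 − 0.975² = 4.94%, bound 5%. Holm has the same 5% bound.
- Fixed sequence: the first outcome is tested at the full 0.05, and overall error is at most 5%.
- Requiring both at 0.05: overall error is at most 5%.

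**5. Power for NT-proBNP at 63 per arm, by the article's formula.** Standardised effect = 0.26 × √(63/0.495) = 2.933.

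- One-sided 0.05: Φ(2.933 − 1.65) = about 90%
- Two-sided 0.05: Φ(2.933 − 1.960) = 83.5%
- Two-sided 0.025: Φ(2.933 − 2.241) = 75.5%

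The formula compares two proportions, whereas section 2.11 plans a t test or a rank-type alternative. These powers compare the options on the article's own basis and do not describe the planned analysis.

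**The case against.** **A joint rule and the choice of decisive set may sit in an unseen analysis plan.** This is fair. The article condenses a fuller protocol, and its silence on multiplicity would not by itself be a finding. It does not cover the marginal band, which is a stated rule that conflicts with section 2.7. An added multiplicity rule would leave that label in place. Naming two primaries, sizing on one and analysing both in two sets are likewise stated choices.

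**The band is not a decision threshold.** This largely stands. A reader might infer that the trial is run at a 19% false positive rate instead of 5%. The documents do not support that. Section 2.11 keeps the unqualified term for P below .05, section 2.7 keeps alpha at 0.05, and nowhere is P < .1 made the criterion for success. The 19% also needs zero correlation, and either two-sided errors counted in both directions or one-sided P values. The main figure is therefore 9.75%, with 19% as the conditional case in which marginal results are read as positive.

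**A claim of benefit is directional.** This stands too. With two-sided P values, the error favouring YLS is about half the either-direction figure. It is still roughly double its own nominal level, 4.9% against 2.5%.

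**Both primaries might be required.** Then having two outcomes would cause no inflation, but the article does not say so.

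**The two analysis sets.** Free choice between them could push the error above the figures given. They overlap heavily and the documents do not allow the addition to be sized, so no number is claimed.

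**Conclusion.** The concern holds in this form. The marginal band contradicts the planned alpha, and the text gives no rule that keeps the primary claim at 5%.

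Within one analysis set, if either primary suffices, the error is up to 9.75% at P < .05, and up to 19% only if marginal results are also treated as positive. For findings favouring YLS with two-sided P values, the corresponding figures are up to 4.9% and 9.75%.

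These sizes rest on assumptions the documents do not settle: that either outcome may carry the claim, the correlation, and the sidedness of P. The direct conflict between sections 2.7 and 2.11 rests on none of them. The bands for P below .01 do not affect the error rate and are not part of this point.

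**What to change.** 1. Delete the marginal band in section 2.11. State that only P < .05 counts, and whether it is one- or two-sided, consistently with section 2.7.
2. Name the intention-to-treat analysis as decisive and the per-protocol analysis as supportive.
3. State one rule for the two primaries. Any of these controls the error at an overall 0.05:
   - Holm;
   - a fixed sequence with NT-proBNP first, because it carries the sample size, and LVEF tested only if NT-proBNP succeeds;
   - success only if both are significant.
4. Report estimates with 95% confidence intervals and exact P values.

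No extra patients are needed for these changes. Both named primaries can stay: demoting LVEF in a registered, ethics-approved trial would change a primary outcome, and is not needed to control the error.

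The cost is power for a claim on one outcome. On the article's formula at 63 per arm, NT-proBNP has 83.5% at two-sided 0.05 (fixed sequence). It has 75.5% at two-sided 0.025 (the first Holm step), which is below the stated 80%. Both compare with about 90% at the one-sided 0.05 implied by 1.65. Under the fixed sequence, LVEF alone can no longer carry a claim. Requiring both makes power depend on LVEF as well, for which the article gives no planning figures.

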### Ethics and dissemination

2.12

This trial has been registered at Chinese Clinical Trial Registry http://www.chictr.org.cn/showproj.aspx?proj=61713. The data of this trial will be managed by ResMan at http://www.medresman.org/ and posted on Chinese Clinical Trial Registry. The results of this study will be disseminated to the public through academic conferences and peer-reviewed journals.

## Discussion

3

Several cardioprotective therapies, which have been conferred robust cardioprotection in experimental animal models of acute ischemia and reperfusion injury, have failed in the clinical setting of AMI for patient benefit.^[25]^ Although the cardioprotective strategies act through common end-effectors, multiple mechanisms affect cardiomyocyte death. The treatments emerging from experimental studies may be suboptimal in patients with comprehensive comorbidities.^[26,27]^ Therefore, additive or synergistic cardioprotective effects of multiple cardioprotective agents might be better cardioprotective strategies to reduce myocardial infarction.^[28]^ As a supplementary and complementary medicine, the characteristics of CHM that is multiple treatment target are attracting more attention. As the principal active components, pharmacological studies have shown that Astragalus membranaceus could perform the function of anti-oxidation, regulation of mitophagy, anti-inflammation, immunomodulatory effects, anti-neurodegeneration.^[29,30]^ Salvia miltiorrhiza is reported to protect vascular endothelial cells against hypoxia, regulate proliferation and migration of VSMCs, improve microcirculatory, and have function of anticoagulant, antithrombotic, anti-inflammatory.^[31]^ Previous studies have shown that Cortex Moutan and Lonicerae japonicae flos both have cardioprotective function^[32,33]^ (Table 1). However, whether the postoperative administration of YLS in AMI patients treated with PPCI will improve cardiac function still requires confirmation by randomized, double-blinded, placebo-controlled, parallel-group clinical trial with the objective of determining the effectiveness and safety of YLS.

This trial tried to incorporate miRNA-145 as one of surrogates for hard clinical endpoints. miRNAs are single-stranded RNA molecules 20 to 25 nucleotides in length coded by genes transcribed by DNA, which are known as “noncoding RNA.” While miRNAs are not converted to protein products, they act to gene expression, primarily through translation repression or RNA degradation.^[34,35]^ Several investigations have demonstrated that miRNAs may play a major role in regulating most of the human genome, including gene alterations associated with various aspects of heart disease, such as ischemic MIR.^[36]^ Genetic or pharmacological manipulation of miRNAs has been indicated to modulate the sensitivity of the myocardium to MIR,^[35]^ protective noncoding RNAs may have a role in the setting of anticipated ischemia.^[37]^ Because of their significant role in all stages of MIR, regulating miRNAs is a promising therapeutic strategy. The miRNAs in plasma and serum are reported that are present in a remarkably stable form and can be detected in the peripheral circulation.^[38]^ Therefore, the miRNAs can be considered as promising novel biomarkers for the diagnosis and prognosis of cardiovascular diseases.^[39]^ Previous studies reported that the expression of miRNA-145 is associated with MIR.^[40]^ In animal model of ischemia/reperfusion injury and myocardial hypoxia/reoxygenation-induced cell model, miRNA-145 were significantly reduced,^[41,42]^ which indicated that the abnormal expression of miR-145 may be the good candidate for MIR.

A potential limitation of our study is that the trial will be undertaken in China, it is uncertain whether the similar effects are available to other ethnic groups and regions. To conclude, the aim of this trial is to demonstrate that YLS will protect the myocardial function in patients with AMI after successful PCI and subsequently yield long-term benefit.

